***Withdrawal criteria***

Withdrawal criteria includes: (1) withdrawal of informed consent or request to withdraw from the study during the observation period; (2) subjects or researchers know the experimental grouping rate is more than 20 %; or (3) PaCO2 ≥ 90mmHg and PH ≤7.15 during the operation.

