**Materials and methods**

This is a prospective, parallel, double-blinded, randomized controlled trial, which will be administered at the Guanyun People’s Hospital.

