***Anesthesia maintenance***

Anesthesia maintenance is defined as the time from the end of induction to the cessation of anesthesia (the infusion or inhalation of anesthetic drugs will be stopped immediately after the end of surgery). Group T will receive continuous propofol infusion at a rate of 4–12 mg/kg/h for maintenance, whereas Group C will receive inhalation of sevoflurane at 1.0-3.0% for maintenance. Remifentanil will be administered at a rate of 0.05–0.2 μg/kg/min, cisatracurium and sufentanil will be added in both groups according to requirements of the surgery. The depth of anesthesia will be titrated to BIS values of 40–55 via the manual adjustment of propofol infusion or inhalation of sevoflurane. Upon completion of the surgery, all anesthetic agents will be discontinued. All patients will be provided with patient-controlled intravenous analgesia (PCIA) (1.5 μg/kg of sufentanil + 0.9% normal saline, total volume 100 ml 2 ml/h for 48 h). The self-controlled capacity and the locking time will be 0.5ml and 15 minutes, respectively.

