***Data collection and registration***

Trained independent investigators who are unaware of group assignment will collect patients’ demographic data and baseline characteristics. The primary and secondary outcome measures as well as other non-outcome perioperative data will be collected. The values of MAP、HR、BIS、ETCO2 and PaCO2 will be recorded at five timepoints: baseline, 30 mins into the surgery, 60 mins into the surgery, the end of surgery, and immediately after tracheal extubation. Postoperative pain will be evaluated using the Numerical Rating Scale, ranging from 0 to 10 (0=no pain, 10=the most severe imaginable pain). Levels of proinflammatory cytokines and NRS will be recorded at postoperative 2,6,24h. All data will be entered into the electronic case report forms(eCRFs) under the supervision of trained research personnel. Investigators will conduct an interim analysis to make an informed decision on whether to continue the trial or modify the study design to optimize the trial results. After the completion of data registration, the electronic database will be locked. After de-identification, the database will be sent to an independent statistician for statistical analysis.

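### Withdrawal criterion (2) sets a trial-level rate of known allocation (above 20%) as a reason to withdraw patients, so it cannot say which patient leaves, and applying it patient by patient would be a post-randomisation exclusion

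*Protocol*

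**What the plan says.** The Withdrawal criteria section of the protocol has three items.

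- Item (1) is "withdrawal of informed consent or request to withdraw from the study during the observation period".
- Item (2) is "subjects or researchers know the experimental grouping rate is more than 20" per cent.
- Item (3) is "PaCO2 ≥ 90mmHg and PH ≤7.15 during the operation".

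For item (2) the protocol gives no denominator, no time or method of assessment and no definition of *researchers*. It does not say whether exceeding the limit removes the patients concerned, removes everyone or stops the trial.

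Three other places bear on it.

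- Materials and methods calls the study a "prospective, parallel, double-blinded, randomized controlled trial" and does not list the blinded roles.
- Anesthesia maintenance gives group T a propofol infusion and group C inhaled sevoflurane, with depth titrated "via the manual adjustment of propofol infusion or inhalation of sevoflurane". No dummy or concealment is described.
- Data collection and registration assigns demographic and baseline data to "Trained independent investigators who are unaware of group assignment". It then says, in the passive voice, that primary and secondary outcomes will be collected.

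**The concern.** A withdrawal criterion has to be decidable for the patient in front of the investigator. Items (1) and (3) are; item (2) is not, because it is a proportion across patients. Staff who try to apply it must invent its meaning, and different staff may invent different ones.

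The most natural patient-level version is to withdraw anyone whose allocation has become known. That is a selection made after randomisation. Appendix A places allocation two hours before surgery, so any disclosure during or after the operation comes later. The primary outcome, QoR-40 on POD 1, is reported by the patient. If the chance of the allocation becoming known is related to treatment and to how recovery went, removing those patients breaks the comparability that randomisation provided. A patient withdrawn before POD 1 may have no primary outcome at all.

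**Working it through.** **1. Level of each criterion**

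| Item | Unit | Decidable for one patient? |
| --- | --- | --- |
| (1) consent or request to withdraw | patient | yes |
| (2) rate of known allocation above 20% | trial | no: for one patient the value is 0% or 100% |
| (3) PaCO2 and pH during the operation | patient | yes |

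Across the trial, 20% of the planned 80 patients is 0.20 × 80 = 16, so the limit is exceeded at 17 patients. Reaching 17 still does not say whether those 17, all 80 or none are withdrawn.

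**2. The two readings of *researchers***

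- *Includes the titrating anaesthetists.* They adjust one of two different agents given by different routes, with no masking described, so they know the group in every case. The rate is 1/1 = 100% after the first patient and 80/80 = 100% at the end. The limit is always exceeded.
- *Means only the blinded data collectors, alongside the patients.* A rate can then be calculated and may stay below 20%. The rule still does not name who leaves, and any patient-level use of it is an exclusion made after randomisation.

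**3. The plan's sample size, reproduced**

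Inputs from Sample size estimation and Statistical analysis: difference 6.3, SD 9.3, two-sided α 0.05, power 80%, dropout 10%.

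- Normal approximation: n = 2(1.960 + 0.842)² × 9.3² / 6.3² = 2 × 7.851 × 86.49 / 39.69 = 34.2, rounded up to 35 per group.
- Two-sample t-test: 35.19, rounded up to 36 per group, as stated.
- Dropout: 36 / 0.90 = 40 per group, 80 in total, as stated. The allowance covers 80 − 72 = 8 patients.

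The sample size is not in dispute.

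**4. Illustration of lost patients**

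Assumption: exactly 17 patients are withdrawn, their QoR-40 is lost, and nobody else drops out. Then 80 − 17 = 63 remain, 31 and 32 per group.

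- Standard error = 9.3 × √(1/31 + 1/32) = 2.34.
- 6.3 / 2.34 − 1.96 = 0.73, so power is about 0.77 by the normal approximation and 0.75 by the t-test.

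| Patients analysed per group | Power (t-test) |
| --- | --- |
| 40 | 0.85 |
| 36 (planned) | 0.81 |
| 32 (16 lost) | 0.76 |
| 31 and 32 (17 lost) | 0.75 |

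**The case against.** The best defence is that item (2) is a poorly worded trial-level check on blinding that was never meant to remove individuals. That may be the intention. But it is listed as a withdrawal criterion with no other procedure attached, so the text does not deliver that check.

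Another defence is that the handling of withdrawn patients in the analysis commonly belongs in the SAP, which is not at hand, and the protocol nowhere says their data are discarded. This stands as a limit on the claim: bias is possible, not demonstrated. It does not rescue the rule, because an SAP cannot turn a trial-level rate into a workable patient-level criterion or restore a QoR-40 score that was never collected.

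A reader might infer more than the document supports.

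- *The rule is triggered at once, for everyone.* This follows only if *researchers* includes the treating anaesthetists, and the protocol does not define the word.
- *Blinding covers baseline data only.* The sentence on outcomes follows directly in the same paragraph and names no other collector. The same blinded investigators are a plausible reading; the text merely leaves it unsaid.
- *The double-blind label is false.* The protocol does not claim that the anaesthetist is blinded. Blinding of patient and assessor is compatible with a common induction and with different maintenance agents given under general anaesthesia.
- *The rule will cost five points of power.* Nothing in the protocol predicts how many allocations will become known.
- *Patients who guess their group from symptoms must leave.* The criterion speaks of knowing, not guessing.

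**Conclusion.** The point holds for the rule as written. Item (2) applies a trial-level rate as a patient withdrawal criterion and cannot determine who is withdrawn; this follows from the text alone and needs no assumption. Its consequence depends on an undefined word: on the broad reading it is met from the first patient, and on the narrow reading any patient-level use is a post-randomisation exclusion that could bias QoR-40. The size of that bias cannot be estimated from the document. Power of about 75% against the stated 80% is an illustration that rests on 17 patients lost and no other dropout. The protocol's double-blind label and its sample size are not shown to be wrong.

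**What to change.** 1. In Withdrawal criteria, delete item (2).
2. State that patients whose allocation becomes known, to themselves or to an assessor, stay in follow-up and in the primary analysis in the group to which they were randomised.
3. Record each such event (who learned the allocation, and when) and report the counts by arm. If the sponsor wanted a check on blinding, this provides it without removing anyone. A question asking patients and assessors to guess the group on POD 1 is an optional addition.
4. In Materials and methods and in Data collection and registration, state that the blinded roles are the patients and those who collect QoR-40, NRS and ward adverse events.

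The cost is a few sentences and one field on the case report form, using visits and independent investigators already planned. No treatment, schedule or sample size changes.

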**Introduction**

Compared with transperitoneal laparoscopic approach, retroperitoneoscopic approach has many advantages in urological surgery, such as shorter puncture path, shorter operative time, less blood loss, less postoperative pain, and faster recovery[1-4]. However, restricted to the retroperitoneal anatomy, the limited working space can make the procedure technically challenging, higher insufflation pressures (20–25 mmHg) of CO_2_ is needed to create a larger working space[5, 6]. More CO_2_ is absorbed into the blood, causing harm to the human internal environment.

Propofol-based total intravenous anesthesia (TIVA) and sevoflurane inhalation anesthesia are two general anesthesia techniques commonly used in clinical practice. Compared with inhalation anesthesia, whether TIVA can provide better postoperative quality of recovery is influenced by the type of surgery[7-9]. The Global Quality of Recovery- 40 (QoR-40) questionnaire was specifically designed to measure the health status of patients after surgery and anesthesia, and it involves 5 dimensions: physical comfort, physical independence, emotional state, psychological support and pain[10]. On the strength of its reliability and validity, QoR-40 has a broad clinical application[11, 12] . Peripheral inflammatory factors can lead to inflammatory reactions such as vasodilation, increased permeability, leukocyte exudation, and even increase the permeability of the blood-brain barrier. Inflammatory factors enter the central nervous system, neurons are damaged or die, resulting in brain tissue damage. By measuring and comparing the levels of perioperative inflammatory factors, we can predict the postoperative recovery of patients[13, 14].

Therefore, the objective of our study is to compare the effects of TIVA and inhalation anesthesia on the quality of recovery by using the QoR-40 questionnaire, and the levels of inflammatory factors in patients undergoing urological retroperitoneoscopic surgery.

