***Outcomes***

***Primary outcomes***

The primary outcome of this study is global Quality of Recovery-40 (QoR-40) score on POD 1. The QoR-40 contains 40 items assessing five dimensions of recovery: emotions, physical comfort, psychological support, physical independence, and pain, which scores range from 40 to 200. QoR-40 has been widely used in clinical practice and research for various surgical types and anesthesia techniques.

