***Secondary outcomes***

The secondary outcomes include QoR-40 score on POD 2 and POD 3, levels of proinflammatory cytokines (tumor necrosis factor-α, interleukin -1β, and interleukin -6), hemodynamic parameters, arterial and end tidal carbon dioxide pressure, pain scores at rest and while coughing, extubation time , length of PACU stay, ramsay sedation score on awakening, awakening time , adverse events (postoperative nausea and vomiting, headache, respiratory depression ,hypoxemia).

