***Sample size estimation***

The primary outcome that will be assessed in this study is the QoR-40 score on postoperative day (POD) 1. Previous studies reported that the minimal clinically important difference (MCID) of QoR-40 score was 6.3 points[10], based on our institutional data, the Standard Deviation was 9.3 points. Based on this assumption, 36 patients in each group would be required with a power of 80% and at an α level of 0.05. To allow for 10% possible dropouts, a total of 80 patients (n = 40 in each group) will be enrolled. The sample size is calculated using the PASS software (version 15.0.5, NCSS, LCC, Kaysville, UT).

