**Appendix A**

| Table 1 Schedule of patient enrolment, study interventions and outcome assessment | | | | | | | | | |
| --- | --- | --- | --- | --- | --- | --- | --- | --- | --- |
|  | Study period |  |  |  |  |  |  |  |  |
|  | Enrolment | Allocation | Post-allocation |  |  |  |  |  |  |
|  |  | 2 hours |  |  |  |  |  |  |  |
|  | Preoperative | before |  |  | POS | POS | POS | POS | POS |
| Time point | visit | surgery | intraoperatively | PACU | 2h | 6h | 24h | 48h | 72h |
| Patient enrolment |  |  |  |  |  |  |  |  |  |
| Eligibility criteria | **×** |  |  |  |  |  |  |  |  |
| Written informed  consent | **×** |  |  |  |  |  |  |  |  |
| Demographic data | **×** |  |  |  |  |  |  |  |  |
| Baseline  characteristics | **×** |  |  |  |  |  |  |  |  |
| Randomisation/ |  | **×** |  |  |  |  |  |  |  |
| allocation |  |  |  |  |  |  |  |  |  |
| Study interventions |  |  |  |  |  |  |  |  |  |
| Total intravenous |  |  | **×** |  |  |  |  |  |  |
| anaesthesia |  |  |  |  |  |  |  |  |  |
| Inhalation |  |  | **×** |  |  |  |  |  |  |
| anesthesia |  |  |  |  |  |  |  |  |  |
| Outcome assessment |  |  |  |  |  |  |  |  |  |
| QoR-40 scores | **×** |  |  |  |  |  | **×** | **×** | **×** |
| Postoperative pain  scores |  |  |  |  | **×** | **×** | **×** |  |  |
| Length of PACU  stay |  |  |  | **×** |  |  |  |  |  |
| Levels of | **×** |  |  |  | **×** | **×** | **×** |  |  |
| proinflammatory |  |  |  |  |  |  |  |  |  |
| cytokines |  |  |  |  |  |  |  |  |  |
| Hemodynamic |  |  | **×** |  |  |  |  |  |  |
| parameters |  |  |  |  |  |  |  |  |  |
| ETCO2 |  |  | **×** |  |  |  |  |  |  |
| PaCO2 |  |  | **×** |  |  |  |  |  |  |
| Awakening time |  |  | **×** |  |  |  |  |  |  |
| Extubation time |  |  | **×** |  |  |  |  |  |  |
| Level of sedation |  |  | **×** |  |  |  |  |  |  |
| PONV |  |  |  |  |  |  | **×** |  |  |
| Headache |  |  |  |  |  |  | **×** |  |  |
| Hypoxemia |  |  |  |  |  |  | **×** |  |  |
| Respiratory depression |  |  |  |  |  |  | **×** |  |  |
| According to SPIRIT statement of defining standard protocol items for clinical trials. | | | | | | | | | |
| QoR-40, 40 items of Quality of Recovery;PACU, post-anaesthesia care unit;  PONV, postoperative nausea and vomiting; POS, postoperative; | | | | | | | | | |
| ETCO2,end-tidal carbon dioxide;PaCO2,partial pressure of arterial carbon dioxide. | | | | | | |  |  |  |
| SPIRIT, Standard Protocol Items: Recommendations for Interventional Trials. | | | | | | | | | |

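### Severe intraoperative hypercapnia with acidosis is a withdrawal criterion after randomisation, and the protocol does not keep these patients in follow-up

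*Protocol*

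**What the plan says.** Item (3) of the Protocol's Withdrawal criteria is "PaCO2 ≥ 90mmHg and PH ≤7.15 during the operation". The list opens with "Withdrawal criteria includes: (1) withdrawal of informed consent or request to withdraw from the study during the observation period", so item (3) stands beside consent withdrawal and apart from the exclusion criteria, which have their own section.

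The timing comes from Appendix A. The schedule header runs "Enrolment | Allocation | Post-allocation", the allocation column is set 2 hours before surgery, and the intraoperative column falls after allocation.

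Secondary outcomes include "arterial and end tidal carbon dioxide pressure". Under Data collection and registration, "ETCO2 and PaCO2 will be recorded at five timepoints": baseline, 30 and 60 minutes into surgery, end of surgery and just after extubation. The Introduction gives the reason for interest in CO2: "More CO_2_ is absorbed into the blood, causing harm to the human internal environment".

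The primary endpoint comes later: "The primary outcome of this study is global Quality of Recovery-40 (QoR-40) score on POD 1". On numbers, Sample size estimation says "To allow for 10% possible dropouts, a total of 80 patients (n = 40 in each group) will be enrolled".

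**The concern.** A randomised comparison is protected only if the people compared are the people randomised. Item (3) makes leaving the study depend on an event that happens under the assigned anaesthetic and is partly a bad value of one of the trial's own outcomes. By comparing PaCO2 between groups, the protocol allows that the anaesthetic might affect it.

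If a patient who meets (3) is taken out before POD 1, the QoR-40 scores on POD 1 to 3 and the 2, 6 and 24 h cytokine and pain values may never be collected. A statistical analysis plan can define the analysis population, but it cannot restore data that were not collected. This is therefore a matter for the protocol text and not a detail left for later.

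Visibility is also at stake. The adverse events named under Secondary outcomes are nausea and vomiting, headache, respiratory depression and hypoxemia. Hypercapnic acidosis is not among them, and pH is not among the values listed for recording at the five timepoints. The event could appear in the report only as a dropout.

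**Working it through.** **1. The plan's own figure.** Inputs from Sample size estimation and Statistical analysis: difference 6.3, SD 9.3, power 80%, two-sided α 0.05.
- Normal approximation: n = 2 × (1.960 + 0.842)² × (9.3/6.3)² = 34.2, so 35 per group.
- Two-sample t-test: 35.19, so 36 per group, as stated.
- Dropout: 36 / 0.90 = 40 per group, 80 in total, as stated.
- Power by t-test is about 81% with 36 per group and about 85% with 40.

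The sample size reproduces, and the point does not depend on it.

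**2. Order of events.** Allocation (2 h before surgery) → possible trigger of (3) (during surgery) → cytokines and pain (2, 6, 24 h) → QoR-40 (24, 48, 72 h). Every postoperative outcome comes after the trigger.

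**3. Shift in the QoR-40 difference if these patients are not analysed.** Let p be the fraction of an arm that meets (3), and D the number of points by which those patients score below the rest of their own arm. The full-arm mean is the retained mean minus p × D. Dropping them therefore moves the T minus C difference by pT × DT − pC × DC. With a common D this is (pT − pC) × D, and the arm with more events is flattered. The protocol gives neither p nor D, so all values below are assumptions.

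| Assumed rates | Assumed D | Size of shift | Share of 6.3 |
|---|---|---|---|
| 1/40 vs 0/40 (2.5% vs 0%) | 10 to 20 | 0.025 × 10 = 0.25 to 0.025 × 20 = 0.5 | 4% to 8% |
| 2% vs 10% | 10 to 20 | 0.08 × 10 = 0.8 to 0.08 × 20 = 1.6 | 13% to 25% |
| 5% in both | 10 in both | 0 | 0% |
| 5% in both | 10 in one arm, 20 in the other | 0.05 × 10 = 0.5 | 8% |

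For scale, the standard error of the planned difference with 36 per group is 9.3 × √(2/36) = 2.2 points.

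**4. PaCO2.** As a simplified illustration, take one normally distributed value per patient, equal SDs, and removal of the top fraction p of each arm. The arm mean falls by φ(c)/(1 − p) SD, with c the (1 − p) normal quantile: 0.060 for 2.5%, 0.109 for 5%, 0.195 for 10%.
- 2.5% vs 5%: a true difference of 0.32 SD appears as 0.27.
- 5% vs 10%: 0.36 appears as 0.28.
- 2.5% vs 10%: 0.68 appears as 0.54.

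This treats withdrawal as depending on PaCO2 alone and discards all of a withdrawn patient's values. The actual criterion also requires low pH, and values recorded before the trigger may be kept, so the real effect could be smaller.

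**The case against.** The strongest reply is that the section lists withdrawal criteria and says nothing more. It does not order recorded values to be discarded, state that follow-up stops, or remove anyone from the analysis. An analysis plan that was not available for this review may analyse everyone as randomised. This stands, and it makes the consequence conditional. It does not answer the point about collection: item (3) is listed beside leaving the study at one's own request, and no section says that these patients continue their assessments.

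Several stronger readings are tempting, and the protocol does not support them.
- **That the highest PaCO2 values are removed by rule.** Both conditions must occur together. A PaCO2 of 90 mmHg or more with pH above 7.15 triggers nothing.
- **That the dropout allowance shows withdrawn patients leaving the analysed set.** Going from 36 to 40 is routine inflation. The section does not tie dropouts to item (3). Nor does the lack of a separate row for withdrawn patients in Appendix A show anything.
- **That the comparison is certainly biased.** Equal rates with equal deficits leave the QoR-40 difference unshifted. The Introduction links CO2 absorption to insufflation pressure, and both groups have the same induction and ventilation settings, so the text gives no mechanism for a large imbalance. The 10% scenario means 4 of 40 patients, that arm's whole dropout allowance. Even 1.6 points is below one standard error.
- **That safety is certainly understated.** Ethical considerations and declarations requires all serious adverse events to be reported, with no exemption for withdrawn patients. An event that qualifies as serious is still captured there.

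Item (3) may also serve as an intraoperative safety stop. The statistical point does not require deleting it.

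**Conclusion.** The point holds in conditional form. As written, the protocol makes an intraoperative event, arising after allocation and partly defined by a secondary outcome, a reason for withdrawal before the primary outcome is measured, and it does not provide for continued follow-up. If these patients leave follow-up or analysis, the worst hypercapnic-acidotic cases are missing from both arms' results. The QoR-40 and PaCO2 comparisons can be biased when the event rate or the prognosis of affected patients differs by arm.

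The size cannot be computed from the protocol. The scenarios in the table range from no shift to 1.6 points, with 0.25 to 0.5 points for a single extra patient in one arm, against a target of 6.3. All rest on assumed rates and deficits, and the event may be rare because both conditions are needed. This is a cheap improvement and does not show that the trial's result would be wrong. It is best made before enrolment, or by prompt amendment, because uncollected data cannot be recovered.

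**What to change.** Reword the Withdrawal criteria so that meeting (3) is not withdrawal from the study. Leave the threshold, and whatever clinical action belongs to it, as they are; nothing is proposed on either. State that patients who meet (3):
- continue the scheduled QoR-40 (POD 1 to 3), cytokine, pain and adverse-event assessments, unless they withdraw consent;
- keep the PaCO2 values already recorded;
- are analysed in the group to which they were randomised.

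Report the number meeting (3) by arm as a safety outcome. This needs the qualifying PaCO2 and pH to be entered on the case report form.

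The cost is a few sentences of protocol text and a small addition to the form. The assessments are already in Appendix A and no extra patients are needed: 36 and 40 per group stay as planned, and analysing all 40 gives about 85% power under the protocol's assumptions. The downside is slightly more variable outcome data.
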